### NIHSS and mRS

The National Institutes of Health Stroke Scale (NIHSS) and the modified Rankin Scale (mRS) are standardized tools for evaluating stroke severity and outcomes. The NIHSS assesses various neurological functions such as consciousness, vision, motor function, sensation, speech, and language. Scores range from 0 to 42, with higher scores indicating more severe impairment [18]. Motor function is specifically assessed through Item 5 (Motor Arm), Item 6 (Motor Leg), and Item 7 (Limb Ataxia). The mRS evaluates disability and dependence in daily activities, ranging from 0 (no symptoms) to 6 (death). In this study, validated Chinese versions of both scales will be used [19]. Assessments will be conducted by two independent neurologists, and if discrepancies arise in their scores, a third senior neurologist will be consulted for the final assessment. All raters will receive comprehensive training before the trial begins, and repeated measurements will be conducted to ensure reliability and accuracy.

### Plans to promote participant retention and complete follow-up {18b}

To enhance participant retention and ensure complete follow-up, we will establish regular communication and engagement with participants, implement flexible scheduling for follow-up visits, and provide reminders through phone calls and messages.

### Data management {19}

This study will employ an electronic data management system (EDMS) with an electronic case report form (eCRF) constructed in accordance with the study protocol. Individuals responsible for data entry will be granted the necessary permissions to enter, modify, and resolve queries. Researchers will have permissions for modification, browsing, query resolution, and verification, whereas data management personnel will be permitted to browse, submit queries, and lock data.

To ensure the authenticity, completeness, and accuracy of the data, it is imperative that all trial records be fully completed with no empty or missing entries. Researchers are required to retain all original participant documents to maintain accurate and timely data. Original documents and medical records must be clear, detailed, and easily identifiable by clinical trial personnel. Data in the eCRF can only be modified by authorized researchers. All original trial data records will be preserved for a minimum of 5 years.

### Confidentiality {27}

Personal information about participants will be collected, shared, and maintained with strict confidentiality throughout the trial. Each participant will be assigned a unique identification number, which will label all study-related documents and data to ensure anonymity. Data will be stored in secure, password-protected electronic databases, and physical records will be kept in locked cabinets accessible only to authorized personnel.

Data sharing will be restricted to the research team and authorized monitors, auditors, and regulatory authorities as required. Any shared data will be de-identified. Electronic data transfers will be encrypted for added security.

Regular audits and data checks will ensure compliance with confidentiality protocols. After the trial, personal data will be securely stored for at least 5 years. Participants’ personal information will not be disclosed in any publications or reports.

### Plans for collection, laboratory evaluation, and storage of biological specimens for genetic or molecular analysis in this trial/future use {33}

Not applicable. This study does not involve the use of biological samples for genetic or molecular analysis.

## Statistical methods

### Statistical methods for primary and secondary outcomes {20a}

Once all participants have completed their assessments, data analysis will commence. To reduce bias, the data analyst will remain blinded during the analysis process. Only participants who strictly adhere to the intervention protocol will be included in the analysis. Data that are missing or deviate from the protocol will be excluded from the analysis.

The primary and secondary outcomes will be combined as dependent variables in the generalized linear model (GLM). First, a univariate analysis of the treatment groups will be performed to determine the unadjusted risk ratio (RR) and odds ratio (OR), along with a 95% confidence interval (CI). Next, continuous variables like the NIHSS score at admission, mRS score, and age will serve as covariates. Categorical variables such as sex, hypertension, diabetes, and prior strokes will be included as factors in the GLM to reduce variance error. If the outcomes show statistical significance for the main effects, interaction effects will be used to assess differences between the groups. Changes in blood biochemical indices will be analyzed using repeated measures ANOVA or mixed-effects models, accounting for measurements taken at baseline, 7 days, 30 days, and 90 days. Changes in inflammatory factors (IL-6, IL-8, TNF-α) from baseline to 7 days will be evaluated using paired *t*-tests or Wilcoxon signed-rank tests, based on data distribution. Sensitivity analysis will use the criterion for severe END, defined as either a 4-point increase in NIHSS or a 2-point worsening in motor function based on a higher threshold. All analyses will be conducted using SPSS (IBM Corp., Armonk, NY, USA), with a significance threshold of *α* = 0.05.

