### Outcomes {12}

The primary outcome of this study will be the END within 7 days. END will be defined as a 2-point increase in the NIHSS score or a 1-point increase in motor function (specifically NIHSS Items 5, 6, and 7) within 24 h to 7 days of AIS onset. To address the potential impact of END severity on the reliability of the primary outcome, we will conduct a sensitivity analysis using a higher threshold: a 4-point worsening in the NIHSS or a 2-point increase in motor function, which will be classified as severe END.

The secondary outcomes of the study will include:Evaluation the rate of good prognosis at 30 and 90 days. Good prognosis will be defined as a modified Rankin Scale (mRS) score of 2 or lower, which indicates either no disability or minor disabilityAssessment of the recurrence rate of symptomatic cardiovascular and cerebrovascular events within 90 daysAnalysis of changes in blood biochemical indices (including liver function, renal function, lipid profile, etc.) before and after treatment, measured at baseline, 7 days, 30 days, and 90 daysExamination of changes in inflammatory factors (interleukin-6, IL-6; interleukin-8, IL-8; tumor necrosis factor-alpha, TNF-α) before and after treatment, assessed at baseline and 7 days

Safety outcomes will be documented by recording the types and frequencies of all adverse events and abnormalities in laboratory tests throughout the study duration. Safety evaluations will include assessments of the patients’ general condition, vital signs, blood routine tests, blood biochemistry, liver and kidney function, coagulation function, and neuroimaging examinations. All participants will undergo assessments before treatment initiation and at the initial treatment milestones of 30 days and 90 days.

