### Methods in analysis to handle protocol non-adherence and any statistical methods to handle missing data {20c}

To address protocol non-adherence, we will define the analysis populations as follows: the intention-to-treat (ITT) population will include all randomized participants who have at least one treatment record and will be used for analyzing the primary outcome. The per-protocol (PP) population will include only those participants who fully adhere to the study protocol without major deviations and will be used for analyzing the secondary outcomes. Experience indicates that dropouts are rare. If the proportion of missing data exceeds 10%, multiple imputation techniques will be employed to ensure the robustness of our study results.

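### The protocol gives two incompatible analysis sets for END: strict adherers only in section 20a, intention-to-treat in section 20c

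*Protocol article*

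**What the plan says.** The primary outcome is fixed in Outcomes {12}: "The primary outcome of this study will be the END within 7 days". Two later sections say who enters its analysis.

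- **Statistical methods for primary and secondary outcomes {20a}:** "Only participants who strictly adhere to the intervention protocol will be included in the analysis". The next sentence adds: "Data that are missing or deviate from the protocol will be excluded from the analysis". Neither sentence is limited to secondary outcomes or to a supportive analysis.
- **Methods to handle non-adherence and missing data {20c}:** its intention-to-treat set "will include all randomized participants who have at least one treatment record and will be used for analyzing the primary outcome". Its per-protocol set, by contrast, is to "include only those participants who fully adhere to the study protocol without major deviations and will be used for analyzing the secondary outcomes". On missing data: "If the proportion of missing data exceeds 10%, multiple imputation techniques will be employed to ensure the robustness of our study results".

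Neither section refers to the other, states an order of precedence, or calls one set a sensitivity analysis. The section on unblinding {17b} states that the design is open label.

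**The concern.** An analyst cannot follow both sections for END. The choice decides which patients count in the headline comparison, and in an open-label trial it should be settled before results are known. Leaving it to a separate analysis plan does not cure this: the protocol already states two rules, and a later document could only pick one.

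The two rules also differ in quality. Restricting to adherers conditions on what happens after randomisation. Section {11b} allows withdrawal when a patient cannot continue the intervention, and a patient who deteriorates early is a plausible candidate. If such exclusions are more common in one arm, the END comparison is no longer protected by randomisation. Blinding the analyst, as {20a} provides, does not repair this, because the selection has happened before the data reach the analyst.

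**Working it through.** **1. The two sections side by side, for END**

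| Randomised patient | {20a} | {20c} |
|---|---|---|
| Adheres, END known | in | in |
| Starts treatment, then deviates, END known | out | in |
| END missing, more than 10% missing overall | out | multiply imputed |
| END missing, 10% or less missing overall | out | no method given |

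The second row conflicts at any level of non-adherence. The third conflicts openly. In the fourth, {20c} is silent, so exclusion under {20a} could stand beside it.

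**2. The plan's own sample size**

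Inputs from {14}: END 13.6% (PI) and 33.3% (AT), two-sided α 0.05, 80% power, 70 per group, 78 after 10% loss.

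- Printed formula with p = (0.136 + 0.333)/2 = 0.2345 and δ = 0.197: n = 2 × (1.96 + 0.84)² × 0.2345 × 0.7655 / 0.197² = 72.5.
- Standard variants give 69 (unpooled variance) and 72 (pooled), so the stated 70 is reproduced closely enough.
- 70/0.9 = 77.8, rounded up to 78. This matches.

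The 10% is described as loss to follow-up. No adherence rate appears anywhere.

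**3. What adherers-only selection could do (assumed exclusions)**

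Set-up: no true effect, 78 per arm, the same true END risk r in both arms, and a share f of END cases in one arm excluded as non-adherent, with nobody else excluded. Two values of r are used: 23.45% (the mean of the two planning rates) and 33.3% (the control rate). In the affected arm the apparent risk is r(1 − f)/(1 − rf), so the apparent risk ratio against the other arm is (1 − f)/(1 − rf). Error rates are from simulating a two-sided pooled z-test at nominal 5%.

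| f | Patients excluded (78·r·f) | Apparent RR | Two-sided error |
|---|---|---|---|
| 0 | 0 | 1.00 | about 5% |
| 10% | 1.8 to 2.6 | 0.92 to 0.93 | 5.8% to 6.1% |
| 20% | 3.7 to 5.2 | 0.84 to 0.86 | 8.7% to 9.7% |
| 30% | 5.5 to 7.8 | 0.75 to 0.78 | 14.0% to 16.6% |

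In each row the first figure is for r = 23.45% and the second for r = 33.3%. Worked case, f = 20%, r = 33.3%: 0.8/(1 − 0.0666) = 0.857. If the affected arm is PI, the bias favours evolocumab; if it is AT, it goes against it.

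**4. What the intention-to-treat analysis costs**

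Assume a share d of PI patients do not adhere and carry the control risk. The PI risk becomes (1 − d) × 0.136 + d × 0.333.

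- d = 10%: 0.1557, and power at 78 per arm is about 73%.
- d = 20%: 0.1754, and power at 78 per arm is about 62%.
- d = 0: about 83%.

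**The case against.** The strongest reply is that the harm is hypothetical. Section {20c} expects few dropouts. END is settled by day 7, and the first doses are due within 1 h of randomisation, so before the endpoint the PI arm carries essentially one extra injection. The simulation removes only END cases and only from one arm; at 10% removed, the error barely moves from its nominal level. All of this stands as a limit on size. None of it removes the contradiction over who is analysed.

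Four stronger readings are tempting, and the documents do not support them.

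- **That the treatment-record condition drops PI patients who decline the injection.** Under {11a} PI patients also take rosuvastatin within 1 h of randomisation. One who refuses only the injection would ordinarily still have a treatment record and stay in the set. The term is undefined and the set is strictly a modified intention-to-treat set, but few patients should be lost this way.
- **That the missing-data rules conflict throughout.** They clash openly only above 10% missing.
- **That adherence is judged over 90 days.** No window is stated in either direction.
- **That the adherers-only analysis is the less powerful one.** By the printed formula, losing a further 10% or 20% of 70 per arm leaves 63 or 56 and power of 74% or 69%. Under the dilution assumption above, intention-to-treat gives about 73% or 62% with all 78 per arm, and about 68% or 57% with 70. Power does not favour intention-to-treat here.

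**Conclusion.** The protocol contradicts itself on the primary analysis set, and this must be resolved before the analysis. The conflict over who is analysed for END holds whatever the rate of non-adherence; the conflict over missing data holds above 10%, with a gap in {20c} at or below that level. Following {20a} would give up the randomised comparison in an open-label trial.

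The size of any bias cannot be derived from the documents. Under the one-arm, END-cases-only assumption with no true effect and 78 per arm, a nominal 5% test has an error of about 6%, 9% to 10%, or 14% to 17% when 10%, 20% or 30% of END cases are excluded. Exclusions balanced across arms, or unrelated to outcome, would do less. The argument for an all-randomised set is validity and does not depend on a gain in power.

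**What to change.** 1. In {20a}, delete the two sentences on strict adherers and excluded data, or relabel them as a supportive per-protocol analysis.
2. State once that END is analysed in all randomised participants in their allocated arm, and make {20a} and {20c} agree.
3. Give one missing-data rule for END that reads the same in both sections and also covers 10% or less missing, for example multiple imputation in place of exclusion.
4. Name the set for the secondary outcomes explicitly. The same all-randomised set is preferable, with per-protocol as supportive.

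This changes wording only; no extra visits or data are needed. The statistical cost is dilution: if non-adherent PI patients carry the control risk, power at 78 per arm falls from about 83% to about 73% at 10% non-adherence and 62% at 20%. The sponsor should accept that openly, since the sample size makes no separate allowance for non-adherence.

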### Objectives {7}

The primary objective of this study is to investigate the effects of PCSK9 inhibitors on END in AIS patients with a history of CHD within 24 h of symptom onset. Secondary objectives include evaluating changes in daily living abilities, recurrence rates of cardiovascular and cerebrovascular events within 90 days, alterations in blood biochemical indices/markers, and variations in inflammatory factors between the two patient groups after treatment.

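### Liver and renal function are compared between arms only in adherent participants, so those who stop study drug because of hepatic or renal harm would probably drop out of the comparison

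*Protocol article*

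**What the plan says.** In the protocol article, section {12} places liver and renal function within the blood biochemistry secondary outcome, measured at baseline and days 7, 30 and 90. Section {7} makes this a between-arm question; one secondary objective is to evaluate "alterations in blood biochemical indices/markers, and variations in inflammatory factors between the two patient groups after treatment".

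Section {20a} names the model: "Changes in blood biochemical indices will be analyzed using repeated measures ANOVA or mixed-effects models". It also fixes who and what enters: "Only participants who strictly adhere to the intervention protocol will be included in the analysis", and "Data that are missing or deviate from the protocol will be excluded from the analysis".

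Section {20c} defines two populations. The ITT population "will include all randomized participants who have at least one treatment record and will be used for analyzing the primary outcome". The per-protocol population holds those who "fully adhere to the study protocol without major deviations and will be used for analyzing the secondary outcomes". On missing data it adds: "If the proportion of missing data exceeds 10%, multiple imputation techniques will be employed".

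Separately, section {12} provides for safety by "recording the types and frequencies of all adverse events and abnormalities in laboratory tests throughout the study duration", and lists liver and kidney function among the safety evaluations. Section {22} has all adverse events documented from enrolment to the end of the study. Neither applies an adherence filter.

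**The concern.** Liver and renal indices are markers of toxicity as well as biochemical outcomes. A rise in transaminases or a fall in renal function is an obvious reason to stop a statin or an added lipid-lowering drug. An analysis set defined by adherence therefore selects on a consequence of the outcome itself. If those who stop have the larger rises, the mean rise is understated in each arm.

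The effect on the between-arm difference depends on who stops. If affected participants stop at similar rates in both arms, the difference shrinks towards zero. If stopping differs by arm, the difference can come out too small, too large or reversed, or appear where true toxicity is equal. Unequal stopping is possible because section {17b} describes the trial as open label. At stake is the only between-arm model that the article states for these indices.

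**Working it through.** **Reading the rules together.** Sections {20a} and {20c} disagree about the primary outcome (strict adherers versus ITT). For secondary outcomes they agree in kind: one requires strict adherence, the other assigns the per-protocol set. The point therefore holds whichever section governs. Section {11b} lists being unable to carry on with treatment among the reasons for withdrawal, but nothing says how stopping for toxicity is classified. Someone who has stopped the drug can hardly be called a strict adherer, so exclusion is likely but not certain. The imputation rule in {20c} fills missing values; it does not bring back participants left out of the set.

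**Inputs.** The document gives no toxicity rates and no figure for this outcome. The one number taken from it is the arm size in section {14}: 70 / (1 - 0.10) = 77.8, rounded up to 78 per arm, which reproduces the stated figure. The rest are assumptions:
- D = 100 IU/L, the ALT rise in an affected participant, with no rise in the others (results scale with D);
- p = share of an arm affected: 10%, 5% or 4%;
- s = share of those affected who are excluded: 0 to 75%.

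**Formula.** Mean rise among those kept in an arm = D × p(1 - s) / (1 - p × s).

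Example: p = 0.10, s = 0.50 gives 100 × 0.05 / 0.95 = 5.26.

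| p | s = 0 | s = 25% | s = 50% | s = 75% |
|---|---|---|---|---|
| 10% | 10.0 | 7.69 | 5.26 | 2.70 |
| 5% | 5.0 | 3.80 | 2.56 | 1.30 |
| 4% | 4.0 | 3.03 | 2.04 | 1.03 |

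**Between-arm difference (PI minus AT), IU/L:**

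| Affected, PI vs AT | True | Both 25% | Both 50% | Both 75% | PI 25%, AT 75% | PI 75%, AT 25% |
|---|---|---|---|---|---|---|
| 10% vs 4% | 6.0 | 4.7 | 3.2 | 1.7 | 6.7 | -0.3 |
| 5% vs 4% | 1.0 | 0.77 | 0.52 | 0.27 | 2.8 | -1.7 |
| 4% vs 4% | 0 | 0 | 0 | 0 | +2.0 | -2.0 |

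The unequal columns come from the first table, for example 7.69 - 1.03 = 6.66 and 2.70 - 3.03 = -0.33.

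**Number of people removed.** 78 × p × s for s = 25%, 50%, 75%: with p = 10%, 1.95, 3.9 and 5.85; with p = 4%, 0.78, 1.56 and 2.34. That is about 2 to 6 PI participants and 1 to 2 AT participants.

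**Precision.** With everyone included and no other variability, the 10% vs 4% case has SDs of 100 × √(0.10 × 0.90) = 30.0 and 100 × √(0.04 × 0.96) = 19.6. SE = √(30.0²/78 + 19.6²/78) = 4.06, so z = 6.0 / 4.06 = 1.48 and two-sided 5% power is about 32%. Real variability in ALT would lower it further.

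**The case against.** The strongest reply is that the harm is captured elsewhere. Adverse events and laboratory abnormalities, liver and kidney function included, are recorded with no adherence filter, and a hepatic signal is usually read from abnormality frequencies rather than from a mean change. This stands, and it confines the point to the modelled secondary comparison. It does not make that comparison sound.

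Second, the mechanism is inferred. Section {20c} removes only major deviations, a permitted discontinuation need not be one, and the exclusion of deviating data in {20a} could mean just the affected values. This stands as uncertainty. However, the strict-adherence sentence in {20a} is about participants and carries no such qualifier, so the natural reading removes the whole person.

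Third, every rate above is assumed, and the reversed results need opposite 25% and 75% exclusion shares for which the document offers no support beyond the open-label design. Section {20c} also expects few dropouts. Agreed: the scenarios show a range, not a forecast. With uncommon toxicity, though, losing a handful of people removes much of the signal.

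Fourth, under equal exclusion the 10% vs 4% bias is 1.3 to 4.3 IU/L, at most about one standard error. That is right, and the test result would seldom change.

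Fifth, values taken after stopping may recover, so including them can dilute on-treatment toxicity. That is a fair caution, but it gives no reason to discard values from before stopping.

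Last, the point is one consequence of a wider adherers-only rule, and correcting that rule would resolve it. True, but toxicity markers are where the selection bears most directly on the outcome itself.

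**Conclusion.** The concern holds. The protocol states an analysis set for the between-arm comparison of liver and renal function that conditions on adherence, and adherence is plausibly affected by the very harm being measured. This is a rule stated in two sections, not a detail left to a statistical analysis plan.

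In the illustration, a true 6.0 IU/L difference is reported as anything from -0.3 to 6.7, and equal true toxicity can appear as a difference of 2.0 in either direction. These figures rest on the assumed rise, affected shares and exclusion shares, and on stopping for toxicity counting as non-adherence. The consequence is a biased estimate for one secondary outcome, not a lost safety signal and probably not a changed significance test. It should be corrected; confidence is medium because the classification of such stops is not spelled out.

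**What to change.** State in sections {20a} and {20c} that the adherers-only, data-exclusion and per-protocol rules do not apply to the liver and renal indices. Analyse them in all randomised participants who received at least one dose, which is close to the ITT population that {20c} already defines for the primary outcome. Use the mixed-effects option already named in {20a}, because repeated-measures ANOVA drops anyone with a missing visit. Include every value actually collected: all those before stopping, and those after stopping where they exist. A per-protocol version can remain as a supplement.

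The cost is two or three sentences and slightly more analysis work, and the harm estimate may look less favourable. No extra patients or visits are needed. Section {26b} secures consent to keep using data after withdrawal, but not continued collection, and {11b} treats being unable to carry on with treatment as withdrawal. Values after stopping may therefore not exist; obtaining them would need a separate change to follow-up, which is not asked for here.

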Key inclusion and exclusion criteria	Ages eligible for study: between 18 and 80 years Sexes eligible for study: both Accepts healthy volunteers: no
	Inclusion criteria: Acute ischemic stroke patients with a History of Coronary Heart Disease within 24 hours of onset
	Exclusion criteria: Hemorrhagic or mixed-type stroke. Cerebral arteriovenous malformations or intracranial tumors. Uncontrolled severe hypertension. History of previous cerebral hemorrhage. Retinal or visceral bleeding within 30 days. Use of PCSK9 inhibitors in the past three months. Impaired consciousness. Known allergy or intolerance to PCSK9 inhibitors or statin components. Pregnancy, lactation, or planning pregnancy within six months. Deemed unsuitable for the trial by the investigator.
Date of first enrolment	1 December, 2023
Target sample size	156
Recruitment status	Recruiting
Primary outcome(s)	END and severe END
Key secondary outcomes	Rate of good prognosis at 30 and 90 days. Recurrence rate of symptomatic cardiovascular and cerebrovascular events within 90 days. Changes in blood biochemical indices and inflammatory factors.

In this context, proprotein convertase subtilisin/kexin type 9 (PCSK9) inhibitors, a novel and potent class of lipid-lowering drugs, are gaining significant recognition. By competitively inhibiting the binding of PCSK9 to low-density lipoprotein receptors (LDLR), they reduce LDLR degradation effectively [15], thus lowering circulating low-density lipoprotein cholesterol (LDL-C) levels. Studies have demonstrated that PCSK9 inhibitors can suppress pro-inflammatory cytokines release [10], reduce endothelial cell apoptosis [16], and inhibit platelet activation [17]. As a result, these inhibitors hold promise in preventing atherosclerosis progression and reducing cardiovascular events. This study aims to assess the effectiveness of PCSK9 inhibitors in lowering the incidence of END among AIS patients with a history of CHD.

The findings of this study will not only elucidate the potential role of PCSK9 inhibitors in AIS patients with a history of CHD but also provide novel insights and directions for the treatment of this specific patient population.

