### Strategies to improve adherence to interventions {11c}

To minimize the risk of missing data, each participant will be furnished with paper reminders containing precise dates and times for all scheduled sessions. Additionally, the investigator will conduct weekly phone calls to prompt participants about upcoming sessions and inquire about their adherence to medication.

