### Follow-up

The follow-up period will start on day 8 after enrollment and continue until day 90, with evaluations on days 30 and 90. Assessments will include concomitant medications, adverse events, physical examinations, laboratory tests, NIHSS and mRS scores, and the occurrence of any recurrent cardiovascular or cerebrovascular events. If a participant experiences an endpoint event (recurrent cardiovascular or cerebrovascular event) during treatment or follow-up, the clinical study will be terminated, and active management will be initiated.

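### The 90-day recurrence outcome is planned as a simple proportion among adherers with missing data excluded, which makes no use of partial follow-up and leaves two sections in conflict on missing data

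*Protocol article*

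**What the plan says.** The registration table (Table 2) lists among the key secondary outcomes: "Recurrence rate of symptomatic cardiovascular and cerebrovascular events within 90 days". Outcomes {12} lists the same endpoint.

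Statistical methods {20a} sets the analysis. "The primary and secondary outcomes will be combined as dependent variables in the generalized linear model (GLM"), and "a univariate analysis of the treatment groups will be performed to determine the unadjusted risk ratio (RR) and odds ratio (OR") with 95% confidence intervals. The same section fixes who is analysed: "Only participants who strictly adhere to the intervention protocol will be included in the analysis". It then adds: "Data that are missing or deviate from the protocol will be excluded from the analysis".

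Section {20c} defines a per-protocol population of participants who adhere fully "without major deviations and will be used for analyzing the secondary outcomes". It also provides for multiple imputation once more than 10% of data are missing, and describes dropouts as rare.

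On what happens at an event, the Follow-up section says: "If a participant experiences an endpoint event (recurrent cardiovascular or cerebrovascular event) during treatment or follow-up, the clinical study will be terminated". I read this as ending the study for that participant.

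No section names a time-to-event or other censoring-aware method. The additional analyses in {20b} mention chi-square tests and logistic regression for categorical and binary outcomes.

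**The concern.** Recurrence within 90 days accumulates over follow-up, and the two kinds of incomplete follow-up are not treated alike. A participant with an event on day 20 has a settled outcome, because the event closes follow-up. A participant who leaves event-free on day 60 has no day-90 status and is excluded, although 60 event-free days were observed. Being in the denominator then depends partly on the outcome.

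The adherence rules can act the same way: a participant with an event need adhere only until the event, an event-free participant for all 90 days. The design is open label and only one arm has two-weekly injections, so unequal loss or unequal exclusion is plausible, though the article gives no figures for it.

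At stake are the absolute 90-day risks and, if loss differs by arm, the between-arm ratio. Observed follow-up is also discarded in an outcome likely to have few events.

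**Working it through.** **Inputs from the article.** 78 participants per group and a 10% loss allowance (Sample size {14}); follow-up to day 90 (Follow-up). The loss step reproduces: 70/0.90 = 77.8, rounded up to 78 per group, 156 in total. The article gives no recurrence rate, so there is no figure for this outcome to reproduce.

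**Assumptions.** True 90-day risk p = 10% (5% to 20% also tried); constant hazard λ = −ln(1 − p); a share d of participants leaves, independently of risk; events before leaving are counted and event-free leavers are excluded.

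**Formula.** Let q be the probability of an event before leaving, for a participant who leaves.

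- Exits spread evenly over 90 days: q = 1 − p/λ = 1 − 0.10/0.10536 = 0.0509.
- All exits on day t: q = 1 − (1 − p)^(t/90), which is 0.0093 at day 8 and 0.0894 at day 80. As t approaches 90, q approaches p.

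Reported risk = [(1 − d)p + dq] / [(1 − d) + dq].

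**Absolute risk at 10% loss, even exits.** (0.0900 + 0.0051)/(0.9000 + 0.0051) = 0.0951/0.9051 = 10.5%, against a true 10.0%. With all exits on day 8 it is 10.09%, on day 80 10.89%.

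**Ratio when the true ratio is 1.00 and loss is 5% in one arm and 15% in the other** (higher-loss arm over lower-loss arm):

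| Exit timing | 5% loss | 15% loss | Ratio |
|---|---|---|---|
| All on day 8 | 10.04% | 10.15% | 1.01 |
| Even over 90 days | 10.24% | 10.80% | 1.05 |
| All on day 80 | 10.42% | 11.40% | 1.09 |
| Limit at day 90 | 0.10/0.955 = 10.47% | 0.10/0.865 = 11.56% | 1.10 |

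With even exits the ratio stays between 1.05 and 1.06 for true risks of 5% to 20%.

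**Equal loss.** At 10% loss in both arms a true ratio of 1.00 stays 1.00. A true ratio of 0.50 (5% against 10%) is reported as 5.27%/10.51% = 0.50.

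**If leavers are removed whatever their event status.** The reported risk is (1 − d)p/(1 − d) = p, so there is no bias under independent loss. The result above therefore depends on counting events seen before exit.

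**Does imputation step in?** {20c} imputes only above 10% missing. Neither a 10% loss in both arms nor a 5%/15% split, which is 10% overall, exceeds that, so exclusion governs in these cases. Above 10%, {20a} says exclude and {20c} says impute.

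**The case against.** A binary risk at a short, fixed horizon is a legitimate target, the article expects dropouts to be rare, and its 10% is a sample-size allowance, not a forecast of unequal loss. The bias is also small beside sampling error. With 8 events among 78 in each arm, the standard error of the log risk ratio is √[2(1/8 − 1/78)] = 0.47, so the 95% interval around 1.00 runs from about 0.40 to 2.53. All of that stands and limits the weight of the point. It does not justify keeping a rule that discards observed follow-up and conflicts with another section.

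Four stronger readings are tempting and are not supported:

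- *Every event is counted, so recurrence must be overstated.* The strict-adherence and per-protocol rules also remove events in non-adherers, and no section says outright that events before withdrawal are kept. The Follow-up section only suggests it.
- *The treatment ratio is biased as planned.* With equal loss it is essentially unbiased.
- *Early exits could push the ratio to 1.12.* Keeping 8 events in each arm and removing 4 and 12 event-free leavers gives 8/74 = 10.8% and 8/66 = 12.1%, ratio 1.12. If the leavers really went early, the remaining participants would need different true risks to yield 8 events in both arms, which contradicts a true ratio of 1.00. At a 10% risk, early exits give about 1.01 and the maximum is about 1.10.
- *Counting a death without recurrence as a non-event is wrong.* With complete follow-up that is exactly the cumulative incidence with death as a competing event. The fair remark is only that the article states no rule for such deaths in this outcome.

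**Conclusion.** The point holds in a limited form. The article fixes an analysis for the 90-day recurrence outcome that makes no allowance for partial follow-up, restricts it to adherers, and states two incompatible rules for missing data above 10%.

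If events before exit are counted, the 90-day risk is overstated by about 5% in relative terms at 10% loss with even exits. A ratio bias needs unequal loss; in the 5% against 15% example it ranges from about 1% to 10% according to exit timing. The recurrence risk, the loss in each arm, its timing and its independence from risk are all assumptions. Because events in non-adherers are discarded too, the net direction in the planned analysis set cannot be stated. This is a modest defect in a secondary outcome and does not touch the primary endpoint analysis.

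**What to change.** State one population and one missing-data rule for this outcome, so that {20a} and {20c} agree. Then analyse it in all randomised participants as time from randomisation to first symptomatic cardiovascular or cerebrovascular event. Censor event-free participants at last contact, treat death without recurrence as a competing event, and report the 90-day cumulative incidence per arm with the risk difference or ratio and its 95% confidence interval. A log-rank or Cox comparison stratified by sex, the randomisation stratum, is optional. The per-protocol proportion can remain as a supporting analysis.

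The cost is analysis wording and slightly more work. Event and last-contact dates can come from the day 30 and day 90 visits, from adverse-event monitoring by visit and phone ({22}), and from existing contact, since "the investigator will conduct weekly phone calls" ({11c}). The downside is a less simple effect measure for one secondary outcome with few events. Censoring at last contact removes this bias only if leaving is unrelated to recurrence risk.
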